### Randomization and Allocation

Eligible participants who sign the informed consent form will be randomly assigned to the acupuncture or placebo group in a 1:1 ratio. Random sequences will be generated by permuted block randomization of block size 2 or 4 using the random allocation tool in R software 4.1 (R Foundation for Statistical Computing). Random sequence generation will be performed, and random sequences will be determined by an independent statistician prior to enrollment. Only the statistician who generates the random sequence will be aware of the full randomization sequence.

Each random sequence will be sealed in an opaque envelope and stored in a double-locked cabinet. The delegated researcher or research coordinator will explain the trial process to the candidate, obtain written informed consent, open the randomization envelope for each participant, and assign them to an appropriate group.

Intervention researchers will perform acupuncture or placebo acupuncture according to their assigned group. The intervention researchers will stay unblinded because the researchers will perform different interventions according to the group. However, the researchers will separate the person and location to maintain anonymization as robustly as possible. The participant, assessor, and statistician will be blinded, and the location where the intervention is performed will be separate from the location where the assessment will be performed. Interventions will be performed in the ward, and assessments will be performed in the operating room.

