### Study Process

After a sufficient explanation of the purpose and methods of this clinical study by a researcher, subjects who voluntarily decide to participate and sign a written consent form will be evaluated for eligibility at the screening visit. Eligible subjects will be randomly assigned to the acupuncture or placebo control group according to randomization. Acupuncture treatment will be performed twice, one day before surgery (V1) and on the day of surgery (V2).

All intraoperative management and outcome assessments will be independently performed by anesthesiologists who are not involved in the acupuncture procedure. All participants will fast for 6-8 hours prior to surgery. After entering the operating room (V3), electrocardiography, pulse oximetry, and monitoring of the partial pressure of end-tidal carbon dioxide (IntelliVue MX550; Phillips North America Corporation) will be performed continuously. Automated oscillometric measurements of blood pressure at 2.5-minute intervals and “train of four” (TOF) (ToFscan; Drager Technologies) assessments will also be performed. Throughout the surgery, these data will be downloaded to personal computers using RS232C cables.

After checking the initial vital signs (heart rate, blood pressure, and oxygen saturation) (P1), anesthesia will be induced intravenously with propofol (1-2.5 mg/kg) and remifentanyl (0.01-0.1 ng/kg/min). Mask ventilation (P2) with desflurane will be performed after the administration of rocuronium (0.6-1 mg/kg). Once the TOF ratio reaches <2, the anesthesiologist will perform tracheal intubation (P3). The lungs of the subjects will then be ventilated with desflurane and oxygen in air (FiO2=0.5), and the tidal volume and ventilation rate will be adjusted to maintain the partial pressure of end-tidal carbon dioxide between 35 and 45 mmHg. An additional venous tube will then be secured (P4).

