### Sample Size

No prior clinical trial has examined the effect of acupuncture on intraoperative blood pressure fluctuations. As acupuncture is applied as an adjunct to propofol-based general anesthesia in this study, sample size estimation is based on a study comparing mean arterial pressure (MAP) variability between remimazolam and propofol anesthesia [19], which reported MAP fluctuations of 26.7 (SD 9.1) mmHg and 19.5 (SD 7.5) mmHg, respectively. Although the interventions differ, this dataset was considered the best available proxy for estimating between-group differences in MAP variability under general anesthesia.

Using these values, 21 participants per group would be required to achieve 80% power with a 2-sided α of .05 when employing the *t*-test modules, considering that this study is a pilot trial. Assuming a 10% dropout rate due to the short follow-up period, the final sample size has been set at 24 participants per group, totaling 48. All calculations are performed using G*Power version 3.1.9.7 (Heinrich-Heine-University Düsseldorf).

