### Statistical Analysis

Both intention-to-treat and per-protocol analyses will be performed, with intention-to-treat being the primary analysis. For per-protocol analysis, the study participants who successfully complete the surgery will be analyzed separately. Successful completion of the surgery is defined as the completion of the scheduled total laparoscopic hysterectomy under general anesthesia without protocol violations, conversion to open surgery, early termination due to intraoperative complications, or major deviations from the anesthetic protocol, such as changes in the anesthetic agents beyond the predefined regimen. For handling missing data, multiple imputations will be performed to obtain estimates and standard errors by setting 10 imputation sets.

The primary endpoint of this clinical trial is the difference between the highest and lowest mean blood pressure measured from anesthesia induction to the postincision period. The Student *t* test will be used to test whether the difference between the 2 groups in the primary endpoint is statistically significant. To account for potential confounding factors affecting the primary outcome, a multivariable linear regression analysis will be conducted. Covariates will include the placebo credibility score (at V1 and V2), anxiety levels (as measured by the STAI and EQ-5D), baseline ward blood pressure (V2), and preoperative blood pressure measured in the holding area prior to operating room entry (V3).

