In this context, the selection of acupoints in the treatment group was based on previous studies demonstrating their physiological relevance in autonomic modulation and cardiovascular regulation. Specifically, PC5, PC6, and KI3 have been widely associated with reductions in perioperative anxiety and stabilization of heart rate variability, while ST36 is well-documented for its influence on vagal activation and blood pressure regulation. SP3 has been included for its role in supporting systemic homeostasis. For the selection of placebo acupoints, the following 3-fold strategy has been considered to minimize specific physiological stimulation: (1) if possible, a sham needle is preferable; (2) points should avoid all recognized World Health Organization acupoints and should not be situated along any known meridian pathways; and (3) anatomical regions are restricted to outside the limbs, where the treatment acupoints are applied. Since the use of nonpenetrating sham needles is not possible due to product discontinuation, the other 2 strategies have been used for the placebo group.

Our study protocol was designed to optimize the timing of acupuncture application, administering stimulation at 2 timepoints, once on the day before surgery and again on the morning of the surgery, which would allow a sufficient lead time before anesthesia induction. This schedule was chosen based on both clinical feasibility and physiological rationale. As patients are routinely admitted the day before laparoscopic hysterectomy, it is practical to deliver acupuncture during the hospital stay without requiring additional outpatient visits. Moreover, this repeated, preoperative approach provides a longer stimulation window than the approach in most prior studies evaluating acupuncture as an anesthetic adjunct, which typically applied stimulation only shortly before or during anesthesia. While the duration remains shorter than long-term outpatient regimens used for chronic hypertension, it represents a balanced and realistic timeframe to allow acupuncture’s physiological effects to manifest before the influence of general anesthetics begins, potentially enhancing its effectiveness in modulating intraoperative hemodynamics.

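### The supportive regression of the primary endpoint adjusts for blood pressures, and probably credibility scores, taken after needling has begun, so it need not estimate the total effect of acupuncture

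*Protocol article*

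**What the plan says.** Study Process fixes when treatment is given: "Acupuncture treatment will be performed twice, one day before surgery (V1) and on the day of surgery (V2").

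Statistical Analysis names an unadjusted Student t test as the test of the primary endpoint, the highest minus the lowest mean blood pressure from induction to after incision. It then adds a multivariable linear regression of the same endpoint, justified as a way to deal with confounding. The covariate list is explicit: "Covariates will include the placebo credibility score (at V1 and V2), anxiety levels (as measured by the STAI and EQ-5D"), and "baseline ward blood pressure (V2), and preoperative blood pressure measured in the holding area prior to operating room entry (V3"). No blood pressure taken before V1 is on the list.

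The Discussion gives the reason for the choice of points: "PC5, PC6, and KI3 have been widely associated with reductions in perioperative anxiety and stabilization of heart rate variability". It credits ST36 with an influence on blood pressure regulation. It also says the two-session schedule was chosen so that physiological effects can appear before the general anaesthetics act.

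**The concern.** Randomisation already balances the arms, apart from chance, on everything that precedes treatment. A variable measured after treatment has started cannot confound the comparison of arms, but treatment can change it. If it does, and the variable is also related to the outcome, holding it fixed changes the question. The coefficient for group then describes what is left of the effect at a given V3 pressure, not the effect of being assigned acupuncture.

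The protocol's own reasoning makes this more than a formality, because it expects acupuncture to act on anxiety and autonomic tone before induction. V3 pressure is read in that window.

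What is at stake is how the adjusted result is read. It is the only adjusted analysis of the primary endpoint that the article describes, and it is presented as confounding control. If it differs from the t test, readers may take the t test to be confounded and prefer the regression, when the two are estimating different quantities.

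**Working it through.** **1. When each covariate is measured, relative to needling**

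| Covariate | What the article fixes | Relation to needling |
|---|---|---|
| V2 ward pressure (called baseline) | Day of surgery | After the V1 session for certain; before or after the V2 session is not stated |
| V3 holding-area pressure | Just before surgery | After both sessions |
| Credibility at V1 and V2 | Visit only | Concerns sessions already allocated; probably rated after needling, but this is not stated |
| STAI, EQ-5D | No visit given | Unknown |

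Statistical Analysis places the V3 reading before entry to the operating room, while Study Process attaches V3 to the time after entry. Both are after needling, so the conclusion does not depend on which is meant.

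For STAI the text points both ways. The Discussion describes it as a measure of baseline anxiety. Outcome Measures uses it for change in anxiety, and Statistical Analysis lists it among the secondary efficacy endpoints.

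**2. The plan's own figure**

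Inputs from Sample Size: "which reported MAP fluctuations of 26.7 (SD 9.1) mmHg and 19.5 (SD 7.5) mmHg, respectively", and a target to "achieve 80% power with a 2-sided α of .05". Allocation: "randomly assigned to the acupuncture or placebo group in a 1:1 ratio".

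- Difference: 26.7 - 19.5 = 7.2 mmHg.
- Pooled SD: sqrt((9.1² + 7.5²)/2) = 8.34. Standardised difference: 7.2/8.34 = 0.863.
- Normal approximation: n = 2 × (1.960 + 0.842)² × (8.34/7.2)² = 21.05 per group, against the stated 21.
- "Assuming a 10% dropout rate due to the short follow-up period": 21/0.90 = 23.3, rounded up to 24 per group, as stated.

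The noncentral t distribution gives 77.9% power at 21 per group and 79.9% at 22. That small rounding matter is separate from this point. What matters here is that the sample size rests on the unadjusted t test and involves no covariates.

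**3. What adjustment for a post-needling variable does**

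Let T be the arm, M the post-needling covariate and Y the endpoint, with M = μ + aT + u and Y = α + δT + bM + e. The total effect is τ = δ + ab. Regressing Y on T and M returns δ = τ - ab. The bias relative to the total effect is therefore -ab. It is zero if a = 0, and its sign depends on the signs of a and b.

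The documents give neither a nor b, so both are assumed below. Take τ = -7.2 mmHg (a smaller swing under acupuncture), outcome SD 8.34, 21 per arm and one covariate with SD 1, over 3,000 simulated trials per row.

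| Shift a (SD) | Slope b (mmHg per SD) | τ - ab | Simulated adjusted estimate | Power of adjusted test |
|---|---|---|---|---|
| 0 | 3 | -7.2 | -7.2 | 83% |
| -0.5 | 3 | -7.2 + 1.5 = -5.7 | -5.7 | 60% |
| -0.8 | 3 | -7.2 + 2.4 = -4.8 | -4.8 | 43% |
| +0.5 | 3 | -7.2 - 1.5 = -8.7 | -8.6 | 91% |

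In these rows the unadjusted estimate stayed between -7.1 and -7.3 mmHg, with power of 76% to 79%.

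A causal slope is not required. Suppose b = 0 but M and Y share an unmeasured cause that contributes 3 mmHg per SD to Y and on which M loads √0.5. The fitted slope on M is then 3 × √0.5 = 2.12. With a = -0.5 the expected adjusted estimate is -7.2 + 0.5 × 2.12 = -6.1; the simulation gave -6.2.

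The first row also shows what a suitable covariate does. When treatment cannot move it, the estimate stays at -7.2 mmHg and power rises slightly.

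**The case against.** The strongest reply is that this is not the deciding analysis. The article names the t test as the test of significance and sizes the trial on it, and it describes the study as a pilot and as exploratory. That stands. A reader might infer that the primary analysis is biased or that a disagreement between the two analyses could not be resolved. Neither follows: the t test does not use these covariates, and the named test governs.

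A second reply concerns size and direction. A reader might infer that the regression is bound to remove part of the effect or to lose a known amount of power. The documents do not support that. The protocol hypothesises stabilisation in both directions, not a lower pressure before induction. It says the short-term effect of acupuncture on pressure fluctuations has not been established. The endpoint is a range, so its slope on the level of V3 pressure is unknown. The figures above follow from the assumed a and b and are not evidence about this trial.

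A third reply is that some timings are unknown. This too stands. It cannot be said that every covariate is post-needling: STAI and EQ-5D may be baseline values, and the timing of the credibility rating within a visit is not given. The certain part is V2 and V3 pressure.

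One defence does not succeed. The Discussion wants to explore whether psychological state moderates the response. Moderation needs an interaction between arm and a pre-treatment value; adding the score as a covariate does not test it.

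**Conclusion.** The point holds for the supportive regression only. V2 and V3 pressure are measured after at least one and after both needling sessions respectively, and credibility probably is post-needling as well. Confounding control is not a valid reason to adjust for them in a randomised trial. If acupuncture shifts these variables, as the protocol's rationale implies, and they are related to the pressure swing, the adjusted coefficient is not the total effect.

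The bias may go either way. Under assumed shifts of 0.5 to 0.8 SD and a slope of 3 mmHg per SD, a true -7.2 mmHg was estimated as -4.8 to -8.6 mmHg; with no shift there was no bias. The documents do not allow a narrower statement. The t test and the 21 evaluable (24 randomised) per group are unaffected, so this is a correction to a secondary model. It should be made before the allocation is unblinded for analysis.

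**What to change.** Amend Statistical Analysis as follows.

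- State that the unadjusted t test is the sole inferential analysis of the primary endpoint, and drop confounding as the reason for the regression.
- Restrict the adjusted analysis to values taken before the first needling: pre-V1 blood pressure and pre-V1 STAI and EQ-5D, where recorded, naming the visit for each. If no pre-V1 pressure exists, drop the pressure adjustment.
- Report any model containing V2 or V3 pressure, credibility, or post-needling STAI only as a labelled exploratory analysis of mediation or blinding.

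The relabelling costs only wording and leaves the sample size unchanged. The replacement covariates are less certain. The article names no pre-V1 pressure for analysis and does not confirm a pre-V1 STAI. By June 2025, 35 of the 48 participants had been randomised, so values not recorded for them before V1 cannot be recovered. The sponsor should check what was collected before fixing the new list.

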In addition to the primary outcome, secondary outcomes will include hemodynamic stabilization time, incidence of hypotension and hypertension, comparison of drug use, and other efficacy endpoints, including STAI scores. Differences between the 2 groups will be compared using the Student *t* test or Wilcoxon rank sum test, unless otherwise specified. The 2 groups will also be compared by estimating the ratio between the blood pressure measured at each timepoint and that measured at V2, using the blood pressure at V2 as the baseline. Because blood pressure is measured repeatedly, it is not possible to assume independence between measurements; thus, generalized estimating equations will be used. To estimate this ratio, measurements will be log-transformed and included in the model. The 2 groups will be compared using the same method for the pulse rate measured at V2 and the pulse rate at each timepoint. To quantify the length of hospitalization in both groups, we will use Kaplan-Meier estimation to estimate the time until 50% of the participants are discharged. The log-rank test will be used to determine differences in the distribution of discharge times between the 2 groups.

The significance level for all analyses is set at .05. All statistical analyses will be performed using SAS 9.4 (SAS Institute, Inc) or R software 4.1 (R Foundation for Statistical Computing).

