Another strength of our design is the inclusion of psychological covariates to explore individual variability in response. Although not a primary or secondary endpoint, researchers have incorporated validated tools, such as the Spielberger STAI and EQ-5D-5L, to assess baseline anxiety and quality of life. These tools enable exploratory analysis of whether the psychological state moderates the physiological effects of acupuncture, helping to distinguish autonomically mediated responses from those influenced by psychological factors. This addresses a common limitation of prior acupuncture trials, which often did not account for patient-level psychological differences.

For our primary outcome, researchers chose absolute thresholds of MAP, rather than relative changes, due to inconsistencies in baseline blood pressure definitions in perioperative settings. Establishing a reliable baseline for relative changes is challenging, as preinduction blood pressure often differs from values obtained during preoperative evaluation [38], and normal blood pressure levels can vary depending on individual conditions and circadian rhythms [39]. Given these limitations, researchers have adopted standardized MAP thresholds: values below 65 mmHg are associated with impaired organ perfusion, while sustained elevations above 80 mmHg may increase the risk of major adverse cardiovascular events [40]. These thresholds align with intraoperative blood pressure management goals, providing a clear rationale for selecting them as our primary outcome measure. This standardization, along with the use of 2.5-minute noninvasive blood pressure monitoring, enables close tracking of blood pressure changes during the highly dynamic early intraoperative phase [41].

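### Comparing blood pressure and pulse as log ratios to the V2 reading fixes the baseline slope at 1; this additional secondary comparison loses precision unless the true slope is near 1

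*Protocol article*

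**What the plan says.** The Statistical Analysis section of the protocol article adds a further between-group comparison, made by "estimating the ratio between the blood pressure measured at each timepoint and that measured at V2". The V2 value thus serves as baseline. Because the readings are repeated within patients, "thus, generalized estimating equations will be used". On scale, it says: "To estimate this ratio, measurements will be log-transformed and included in the model". Pulse is handled alike: "The 2 groups will be compared using the same method for the pulse rate measured at V2 and the pulse rate at each timepoint".

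No baseline covariate is named for this model. Ward pressure at V2 and holding-area pressure at V3 do appear as covariates in the same section, but only in the supporting multivariable regression of the primary endpoint.

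Three other places bear on the point:
- Outcome Measures lists systolic, diastolic and mean pressure at each timepoint as secondary outcomes.
- Study Process places the first needling session at V1, the day before surgery, and the second at V2, the day of surgery.
- The Discussion explains why relative change was not used for the primary outcome, noting that "preinduction blood pressure often differs from values obtained during preoperative evaluation".

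**The concern.** Dividing by baseline assumes that a patient whose log pressure at V2 is one unit higher will also be one unit higher at every intraoperative timepoint. V2 is a ward reading in an awake patient. The later readings are taken under general anesthesia, with drugs adjusted to hemodynamics. A slope of exactly 1 between the two is possible, but nothing in the document supports it.

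If the slope is below 1, subtracting the whole of log V2 adds variation from the ward reading to each timepoint's comparison. Any chance imbalance in V2 between two small arms also enters the estimate at full weight. What is at stake is the width of the intervals for timepoint-specific pressure and pulse, which are meant to show where in the early operation acupuncture acts.

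**Working it through.** The protocol gives no precision or power figure for these comparisons, so there is none to reproduce. Its 21 per group (24 after dropout) is for the primary endpoint and has no bearing here.

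**Inputs from the document:** ratio to V2, log scale, GEE, no baseline covariate named, 48 patients allocated 1:1.

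**Assumed, because the document does not give them:** rho, the correlation of log V2 with the log value at a timepoint; and k, the SD of the log intraoperative value divided by the SD of log V2. The true slope is then rho × k.

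**Step 1. Form.** log(BP_t / BP_V2) = log BP_t − 1 × log BP_V2, so the baseline coefficient is 1. If V2 is instead entered as the first outcome in a GEE with group-by-time means, the contrast is again the between-arm difference in mean log change. In simulated balanced data (24 per arm, exchangeable working correlation) the two agreed in every fit checked.

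**Step 2. Variances**, in units of the variance of log V2:
- ratio: 1 + k² − 2·rho·k
- baseline as covariate: k²(1 − rho²)
- difference: (1 − rho·k)²

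The difference is never negative and is zero only when the slope rho·k equals 1. This is the large-sample result and ignores the degrees of freedom spent on the covariate.

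**Step 3. Equal SDs (k = 1).** The variance quotient, ratio over covariate-adjusted, is 2(1 − rho)/(1 − rho²) = 2/(1 + rho). The power column is Φ[(1.960 + 0.842)/√quotient − 1.960], the power of the ratio form where the adjusted analysis would have 80%. It is illustrative only.

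| rho | Quotient 2/(1+rho) | SE larger by | 48 patients worth | Illustrative power | Ratio vs no baseline, 2(1−rho) | No baseline vs adjusted, 1/(1−rho²) |
|---|---|---|---|---|---|---|
| 0.2 | 1.67 | 29% | 29 | 58% | 1.60 | 1.04 |
| 0.3 | 1.54 | 24% | 31 | 62% | 1.40 | 1.10 |
| 0.5 | 1.33 | 15% | 36 | 68% | 1.00 | 1.33 |
| 0.7 | 1.18 | 8% | 41 | 73% | 0.60 | 1.96 |
| 0.9 | 1.05 | 3% | 46 | 78% | 0.20 | 5.26 |

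Simulation with 24 per arm gave quotients of 1.50, 1.33 and 1.14 at rho 0.3, 0.5 and 0.7, against 1.54, 1.33 and 1.18 from the formula.

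**Step 4. Unequal SDs, rho 0.2 to 0.9.**
- k = 0.75: the quotient lies between 1.79 and 2.34. At rho 0.2 it is (1 + 0.5625 − 0.30)/(0.5625 × 0.96) = 1.2625/0.54 = 2.34; at rho 0.7 it is 0.5125/0.2869 = 1.79.
- k = 1.25: it lies between 1.00 and 1.38. At rho 0.2 it is 2.0625/1.5 = 1.38. At rho 0.8 the slope is 0.8 × 1.25 = 1 and the quotient is 0.5625/0.5625 = 1.00.

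**Step 5. Against ignoring baseline.** 1 + k² − 2·rho·k exceeds k² when rho·k is below 0.5. In that range, dividing by V2 is less precise than not using it at all.

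**Step 6. Timing of V2.** Suppose the session at V1 shifts log V2 by e and the effect on the log intraoperative value is tau. The ratio then estimates tau − e, and adjustment for V2 estimates tau − slope × e. Only a reading from before the first session is free of this.

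**The case against.** - **The ratio is an additional comparison.** Pressures at each timepoint are listed as outcomes in their own right, and the default test for secondary outcomes is a t test or Wilcoxon test. This stands: the ratio is not shown to be the only route to a timepoint result. At low correlation an unadjusted comparison comes close to the covariate form (1.04 at rho 0.2). It falls well behind at higher correlation (1.96 at rho 0.7), so it does not replace adjustment.
- **The model is only sketched.** A GEE with V2 means constrained to be equal across arms would recover the precision and still yield a ratio, and an analysis plan not at hand may say so. This is why the point is put as the text reads; nothing in the protocol states such a constraint.
- **The size is unknown.** This stands. A reader might infer that every interval is widened materially. The documents do not support that: with k = 1.25 and rho near 0.8 the loss is nil.
- **The Discussion does not show low correlation.** A reader might take its remark on preinduction and preoperative pressure as evidence of a weak relation. It concerns differing levels, and it explains a choice made for the primary outcome only.
- **Change relative to baseline is a legitimate quantity.** This also stands. The protocol itself defines hypotension and hypertension partly as 80% and 120% of baseline. A reader might infer that the ratio form biases the randomised comparison; the form alone does not. The question in Step 6 comes from the timing of V2 and is separate.
- **The trial is called a pilot and exploratory.** That limits the weight of the point, but the improvement costs almost nothing.

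**Conclusion.** The point holds as one of precision in an additional secondary analysis. As written, the blood pressure and pulse comparisons fix the log-baseline slope at 1. Entering log baseline as a covariate is at least as precise in large samples and keeps a ratio scale.

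Under equal log variances the variance is 1.67 to 1.18 times as large for rho from 0.2 to 0.7. Allowing the SD ratio to run from 0.75 to 1.25 and rho from 0.2 to 0.9, it runs from 1.00 to 2.34 times. Both rho and the SD ratio are assumptions, so no single figure can be attached to this trial.

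The primary endpoint and its sample size are unaffected. The change is worth making, but the validity of the trial does not depend on it.

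**What to change.** In Statistical Analysis, replace the ratio-to-V2 comparison with a GEE for log pressure at the intraoperative timepoints, and likewise for log pulse. Its terms should be group, timepoint, group-by-timepoint, log baseline of the same variable, and log baseline-by-timepoint. Report the exponentiated group contrast at each timepoint as the between-arm ratio of geometric means. Show ratios to baseline by arm descriptively.

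For the baseline covariate, use a reading taken before the first session at V1 if one is already recorded. The visible text does not say whether it is, and 35 of the 48 patients had been randomised by June 2025, so this has to be conditional. Otherwise use V2 and state that it follows the first session.

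The cost is a revision of the analysis wording, best made before allocation is revealed to the analyst, and a few degrees of freedom in a small trial. No new data or patients are needed.
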